### Trial design

This study is nested in Project MIND, a cluster randomised controlled trial across 24 public primary care facilities.^24^ Myers *et al*
24 describe the trial in detail. The trial will compare the effectiveness of treatment as usual (MIND_TAU) and two alternative methods for integrating a psychosocial intervention into the primary care services for HIV and diabetes. Treatment as usual (TAU) is representative of typical primary care level services for CMD in the South African public health service facilities, which is typically limited to referrals.^25 26^ The two models will be the dedicated and designated models of care. In the dedicated approach (MIND_DED), community health workers (CHWs) will be hired and added to the facility staff complement and will dedicate their time to *only* delivering the new counselling service. In the designated approach (MIND_DES), CHWs already working in the facility will be designated to deliver the service *in addition* to their other chronic disease-related activities such as adherence counselling for HIV and health promotion. Supervision and debriefing of all the counsellors in the active arms will be task-shifted to registered psychological counsellors in line with the national mental health policy framework.^27^ Descriptions of the CHWs and registered psychological counsellors roles in the MIND-DED and MIND-DES models and their qualifications and skills levels are detailed in the trial protocol.^24^

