#### Sample size and patient population

Recruitment will be restricted to consenting adult patients who meet criteria for hazardous alcohol use or depression using the AUDIT or CES-D. These patients are already diagnosed and receiving treatment for diabetes or HIV, but not currently receiving treatment for a CMD. The trial requires a sample size of 1200 patients (600 with HIV and 600 with diabetes) to detect reductions in hazardous alcohol use and risk of depression at 12-month follow-up. The sample size calculations are based on a cluster randomised design with two active arms and a control arm. This clinical trial is powered to detect clinical outcomes, specifically reductions hazardous/harmful alcohol use and risk of depression at 12-month follow-up rather than economic outcomes.^24 35^

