### Analyses

#### Statistical analysis of costs and effects

Mean provider costs and patient costs will be calculated from baseline until the end of the intervention period. In addition, we will explore the extrapolation of costs to later periods if data allow for this. Cost differences between the MIND-TAU, and the MIND-DES and MIND-DED alternatives will be calculated. Sampling uncertainty for cost data will be estimated using statistical methods that account for the non-normal distribution of costs. Effect in terms of CES-D, AUDIT, HIV viral load, HBA1c and the QALY will be analysed using linear regression on intervention type.

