#### Sensitivity analyses

The decision analytical models will allow for univariate and multivariate sensitivity analyses to be conducted. This will enable the robustness of study findings to be tested by varying key parameters such as utilisation rates and assessing the impact on cost-effectiveness results. Standard areas of analytical focus will be considered, including testing sensitivity around the resource cost and prices, and theoretical controversies,^49^ for example, TTO weights^50^ and discounting of outcomes.^36^ Further analyses to inform the economics of task-sharing will include sensitivity analysis focused on economies and diseconomies of scale and scope, using detailed data from the TMT.^51^ This will include testing variations in staff hours worked, variations in staff mix, lay counsellor funding models and infrastructure investments. The impact of intervention dosage on outcomes will also be assessed in the sensitivity analyses. Statistical methods including multiple imputation will be used to manage the effect of missing information on costs and effects.^52^ These sensitivity analyses are summarised in table 2. Probabilistic sensitivity analysis (which allows application of CIs to point estimates) will be used for sensitivity analyses of all relevant individual-level variables. The sensitivity analyses will be used to produce a cost-effectiveness acceptability curve.

**Table 2 T2:** Planned sensitivity analyses

	Base case	Range
Simple sensitivity analysis		
Discount rate	3%	0%–10%
QALYs: HRQoL weights	EQ-5D valued using UK TTO	EQ-5D valued using Zimbabwe TTO
Unit costs	Primary data and data from published sources and official statistics for South Africa	Varied within plausible ranges as determined from a literature review of South African cost studies
Missing data	Multiple imputation	Complete case analysis
Probabilistic sensitivity analysis		
Intervention utilisation data	Mean value	95% uncertainty interval
Referral service utilisation data	Mean value	95% uncertainty interval
EQ-5D/CES-D/AUDIT data	Mean value	95% uncertainty interval
Clinical outcomes (HbA1c, HIV-1 RNA)	Mean value	95% uncertainty interval

AUDIT, Alcohol Use Disorder Identification Test; CES-D, Centre for Epidemiological Studies scale on Depression; EQ-5D, EuroQol-5D; HbA1c, haemoglobin A1c; HRQoL, health-related quality of life; QALY, quality-adjusted life year; TTO, time trade-off.

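### The trial randomises 24 clinics, but the stated regression for QALYs and clinical effects has arm as its only named term and takes no account of clinic

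*Protocol article*

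**What the plan says.** All of this is in the Protocol article.

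- **Design.** Under Trial design, the study is nested in "a cluster randomised controlled trial across 24 public primary care facilities", with two active arms and treatment as usual.
- **Sample size.** Under Sample size and patient population: "The trial requires a sample size of 1200 patients (600 with HIV and 600 with diabetes"). The same section adds: "The sample size calculations are based on a cluster randomised design with two active arms and a control arm".
- **Effects.** Under Statistical analysis of costs and effects, one sentence covers CES-D, AUDIT, HIV viral load, "HBA1c and the QALY will be analysed using linear regression on intervention type".
- **Costs.** A separate sentence in that section reads: "Sampling uncertainty for cost data will be estimated using statistical methods that account for the non-normal distribution of costs". It names no method.
- **Uncertainty.** Under Sensitivity analyses, the probabilistic analysis "will be used for sensitivity analyses of all relevant individual-level variables". Table 2 lists "EQ-5D/CES-D/AUDIT data", HbA1c, HIV-1 RNA and utilisation among its inputs, each with a mean and a 95% uncertainty interval. The section closes: "The sensitivity analyses will be used to produce a cost-effectiveness acceptability curve".

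The sections on statistical analysis, determining cost-effectiveness and sensitivity analyses mention no clinic effect, multilevel model, cluster-robust variance or resampling of clinics.

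**The concern.** Patients of one clinic share staff, counsellors and catchment population, so their outcomes tend to be correlated. When clinics are randomised, the precision of a comparison between arms depends mainly on the number of clinics. A regression with arm as its only term treats the patients as independent and so overstates that precision.

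The design and sample size recognise the clustering; the stated effect analysis does not. The QALY matters most here. This article is where its regression is specified, and under Determining cost-effectiveness the cost per QALY is what is compared with a threshold. At stake is how firmly the evaluation can say that either counselling model offers value for money. Chance differences between a few clinics per arm could be presented as well-estimated effects.

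**Working it through.** **Inputs from the document:** 24 clinics, 3 arms, 1200 patients (600 HIV, 600 diabetes).

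**Assumptions:** equal allocation and equal clinic sizes; both diseases recruited equally in every clinic; ICC of 0.01, 0.02 or 0.05, because the article gives none.

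The figure of 1200 cannot be reproduced. The article states no significance level, power, effect size, standard deviation, ICC or dropout, and cites the separate trial protocol.

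**Step 1: cluster sizes.** 24/3 = 8 clinics per arm; 1200/24 = 50 patients per clinic (m); 600/24 = 25 per clinic for outcomes of one disease.

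**Step 2: formulas.**
- Design effect: DE = 1 + (m − 1) × ICC.
- Factor by which the naive standard error is too small: √DE. The naive interval has 1/√DE of the correct width.
- True rejection rate of a nominal two-sided 5% test: 2 × [1 − Φ(1.96/√DE)].

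Example with m = 50 and ICC = 0.02: DE = 1 + 49 × 0.02 = 1.98; √1.98 = 1.41; 1/1.41 = 0.71; 2 × [1 − Φ(1.96/1.407)] = 16.4%.

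**Step 3: results.**

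| Outcome | ICC | DE | √DE | Naive width / correct width | Rejection rate of 5% test |
|---|---|---|---|---|---|
| QALY, CES-D, AUDIT (m = 50) | 0.01 | 1.49 | 1.22 | 82% | 10.8% |
| | 0.02 | 1.98 | 1.41 | 71% | 16.4% |
| | 0.05 | 3.45 | 1.86 | 54% | 29.1% |
| HbA1c, viral load (m = 25) | 0.01 | 1.24 | 1.11 | 90% | 7.8% |
| | 0.02 | 1.48 | 1.22 | 82% | 10.7% |
| | 0.05 | 2.20 | 1.48 | 67% | 18.6% |

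For m = 50, a nominal 95% interval would therefore cover about 89%, 84% or 71%. With ICC = 0 nothing is lost. Unequal clinic sizes would raise the design effect.

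**Step 4: check by simulation.** For each ICC, 20,000 null two-arm comparisons were simulated with 8 clinics of 50 patients per arm. The naive test rejected 10.8%, 16.4% and 29.2% of the time at ICC 0.01, 0.02 and 0.05. A t test on clinic means (14 degrees of freedom) rejected 5.0%, 4.9% and 5.1%.

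**The case against.** The strongest defence is condensation. The sentence on effects is a summary that names a model family and the exposure. It does not say that patients are treated as independent, and linear regression with a cluster-robust variance would fit its words. The trial protocol, not shown here, may deal with clustering for the clinical outcomes. This stands as a reason to read the authors' intention generously, but it does not remove the point. The article states a method, that method as worded does not match the unit of randomisation, and the section does not refer the reader to the trial's own models. Whether clinic enters the imputation model, by contrast, is a detail an article may fairly leave out, and it is not pressed.

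A reader might also infer several stronger claims that the document does not support:

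- **That costs are analysed by linear regression on arm.** They have their own sentence, with unnamed methods for non-normal data; a clinic-level bootstrap is not excluded. All that can be said is that clustering is not mentioned.
- **That costs suffer most, because Table 1 allocates many of them by facility headcount.** Table 2 puts unit costs in the simple sensitivity analysis, with ranges from a literature review. Drugs and tests are valued at national prices. The article does not say whether unit costs are applied clinic by clinic or averaged.
- **That the acceptability curve is certain to be wrong.** Table 2 does not say how its intervals are obtained, so the link from the regression is conditional. Sizing the shift would also need an ICC for net benefit and a three-strategy calculation.
- **That intervals will be far too narrow.** At ICC 0.01 they are 10% to 18% too narrow; only the higher assumed values justify stronger words.

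Finally, the decision rule compares a ratio with a threshold and is not a significance test. The rejection rates above are a yardstick for overconfidence and not the error rate of a planned economic test.

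**Conclusion.** The point holds for the effects. The QALY, CES-D, AUDIT, viral load and HbA1c are to be regressed on arm alone in a trial of 24 randomised clinics. Taken literally, that understates the standard errors for any positive ICC. The direction does not depend on the assumptions, but the size does: a factor of about 1.22 to 1.86 for outcomes measured in all patients and about 1.11 to 1.48 for HbA1c and viral load, over an assumed ICC of 0.01 to 0.05 with equal clinics.

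For costs, the finding is limited to silence on clustering. For the Table 2 intervals and the acceptability curve, overconfidence follows only if they are built from these unadjusted estimates. This should be corrected before analysis: the QALY result carries the policy conclusion, and the error runs in one direction.

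**What to change.** In Statistical analysis of costs and effects:

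1. Replace the regression on arm with a linear mixed model that has a random clinic effect and small-sample degrees of freedom (Kenward-Roger or Satterthwaite). Alternatively, analyse clinic means; across all three arms this leaves 24 − 3 = 21 degrees of freedom.
2. For costs, name a method that handles both skewness and clustering, such as a clinic-level or two-stage bootstrap.
3. Under Sensitivity analyses, state that the probabilistic draws and the acceptability curve come from these clustered estimates.

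The cost is a change of wording and the use of standard software. Intervals will be wider and the acceptability curve flatter. No new data are needed.

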#### Determining cost-effectiveness

The analysis will be conducted in line with the Consolidated Health Economic Evaluation Reporting Standards guidelines.^47^ Decision analytical models^37^ integrating the cost and outcomes of the different intervention alternatives will be developed to assess cost-effectiveness. As a meaningful impact of the MIND-DES and MIND-DED on both costs and effects is anticipated, ICERs will be estimated in terms of incremental cost per natural unit and/or intermediate outcome for the CEA, and incremental cost per QALY gained for the CUA. As the trial is focused on health systems strengthening for the delivery of mental health services, the decision rule applies to maximising health within the healthcare budget constraint. Therefore, ICERs will be calculated from the provider perspective and, the cost per QALY gained will be compared with the cost-effectiveness thresholds (CETs) for LMIC settings.^48^ If our intervention’s ICER is less than the chosen CET, this will mean that diverting resources to the intervention will increase population health, and if the ICER is more than the CET the intervention is not cost-effective. Patient costs will be collected and reported on separately. In addition, to satisfy the requirements of common guidelines^47^ and to allow for some degree of comparability with other studies, the ICERs will also be presented for the societal perspective, that is, including both provider and patient costs.

#### Sensitivity analyses

The decision analytical models will allow for univariate and multivariate sensitivity analyses to be conducted. This will enable the robustness of study findings to be tested by varying key parameters such as utilisation rates and assessing the impact on cost-effectiveness results. Standard areas of analytical focus will be considered, including testing sensitivity around the resource cost and prices, and theoretical controversies,^49^ for example, TTO weights^50^ and discounting of outcomes.^36^ Further analyses to inform the economics of task-sharing will include sensitivity analysis focused on economies and diseconomies of scale and scope, using detailed data from the TMT.^51^ This will include testing variations in staff hours worked, variations in staff mix, lay counsellor funding models and infrastructure investments. The impact of intervention dosage on outcomes will also be assessed in the sensitivity analyses. Statistical methods including multiple imputation will be used to manage the effect of missing information on costs and effects.^52^ These sensitivity analyses are summarised in table 2. Probabilistic sensitivity analysis (which allows application of CIs to point estimates) will be used for sensitivity analyses of all relevant individual-level variables. The sensitivity analyses will be used to produce a cost-effectiveness acceptability curve.

**Table 2 T2:** Planned sensitivity analyses

	Base case	Range
Simple sensitivity analysis		
Discount rate	3%	0%–10%
QALYs: HRQoL weights	EQ-5D valued using UK TTO	EQ-5D valued using Zimbabwe TTO
Unit costs	Primary data and data from published sources and official statistics for South Africa	Varied within plausible ranges as determined from a literature review of South African cost studies
Missing data	Multiple imputation	Complete case analysis
Probabilistic sensitivity analysis		
Intervention utilisation data	Mean value	95% uncertainty interval
Referral service utilisation data	Mean value	95% uncertainty interval
EQ-5D/CES-D/AUDIT data	Mean value	95% uncertainty interval
Clinical outcomes (HbA1c, HIV-1 RNA)	Mean value	95% uncertainty interval

AUDIT, Alcohol Use Disorder Identification Test; CES-D, Centre for Epidemiological Studies scale on Depression; EQ-5D, EuroQol-5D; HbA1c, haemoglobin A1c; HRQoL, health-related quality of life; QALY, quality-adjusted life year; TTO, time trade-off.

### Budget impact analysis

There is an increased demand from decision makers in both LMIC and HIC settings for estimates of the real fiscal implications of investing in health services within a defined budget and budgetary period.^53 54^ Trial-based estimates of intervention uptake and population-based estimates of numbers in need of the intervention will be used in budget impact approximations,^55^ which will be conducted using a mathematical programming approach.^56 57^ Mathematical programming provides a useful equity lens for informing policy decisions around the provision of care in high burden, high cost contexts.^58^ It will involve analysing alternative implementation strategies with differing equity implications subject to a budget constraint. This approach aims to support policy making by applying principles of constrained maximisation in resource allocation.^58^ The estimates from this study will inform policy-level discussions on the fiscal implications of investing in primary care mental health services.

## Ethics and dissemination

In the CEA we foresee minimal risks to participants, as patient level data will be collected through the main trial, where, in order to minimise the risk of improper disclosure of information study staff will be required to sign a staff confidentiality agreement and will be trained and certified in protecting human participants. Data collection for the trial will be conducted using Computer-Assisted Personal Interviewing (CAPI) in which only a unique study identifier is used. Knowledge translation will be through policy briefs, and social media as well as peer-reviewed papers, and presentations at health economics and mental health policy conferences. Engagement with department of health policy makers and other key stakeholders will be through a policy dialogue workshop linked to the main trial’s Stake Holder Advisory Group. Dissemination of results to the public will be through press briefings in national and local media.

## Discussion

The delivery of psychotherapy using varying models of task-sharing to less specialised health workers in primary care has been shown to be cost-effective in HIC settings across a range of mental health conditions^59–61^ but has limited empirical economic evidence in LMICs.^51 62 63^ This study will provide evidence to address this gap. Through the CEA, the relative efficiency of each delivery mechanism will be established, enabling a discussion around which model produces the best outcomes given the available resources. As staff time is expected to be one of the main drivers of costs due to the nature of the intervention, we have developed a time tool that will allow us to directly measure staff time usage and investigate any potential excess capacity (hypothesized to occur with the MIND-DED counsellors), and scope economies (hypothesized to occur with the MIND-DES counsellors), which would impact the comparative efficiency of the different alternatives and thus the cost-effectiveness results, as suggested in a similar study.^51^ The CUA will aid health service planners in their decision making around resource allocation and may be useful for guiding priority setting decisions both within the mental health budget space and across competing health priorities. To further support policy maker decisions, the affordability of implementing the intervention will need to be assessed, this will require further analysis using trial-based evidence on intervention uptake and estimates of population-level numbers in need to approximate the budget impact of equitably implementing the service.^58^

Policy discussions on the integration of services to provide holistic care for patients requires economic evidence to support implementation in resource-limited contexts.^4 23^ By estimating the full economic costs of integrating the mental health treatment into the primary care offering for patients with chronic physical diseases, this study will provide much needed economic evidence to support this policy narrative.^4 64 65^ Empirical data on the costs of upskilling and training staff to deliver the intervention and the time costs of the alternative human resourcing strategies will also aid in understanding how this cadre of staff organise their work and may highlight opportunities for efficiency gains. This is timely in the current policy window where the idea of a ’facility counsellor' is being discussed, whose role may span a range of counselling duties including: adherence counselling for TB/HIV, chronic non-communicable physical diseases and mental health counselling. The integration of services is a key health systems focus^66^ requiring economic evidence.^23^ The integration of services at the primary care level^67^ to manage communicable and non-communicable chronicity is a global challenge^20 22 68 69^ and a key strategic aim of the Department of Health^70^ for expanding access to mental health services and managing chronic diseases in South Africa.^27 70^ Brief interventions for depression and alcohol use disorders lack a common outcome measure for use in CEA,^71^ thus limiting comparison across interventions.^72^ This study will provide unique cost-effectiveness evidence using the QALY as an outcome measure for such interventions in the South African context.^51^ This will allow comparability of cost-effectiveness results^73^ and inform value for money decision making.^48 74^ This is of particular importance for South Africa as discussions around cost-effectiveness thresholds^74^ are being increasingly presented in the health policy space in the prelude to National Health Insurance. This protocol also responds to the call to publish health economics protocols alongside trial protocols to reduce publication bias of randomised controlled trial results.^75^

Potential challenges to this study include recall bias due to the reliance on patient-reported health service use for our estimations of service utilisation. To limit recall bias, a 1-month recall period will be used for ambulatory services and 6-month recall for hospitalisations.^52^ Another possible limitation is that only a few patients may be referred for mental healthcare for CMD in the TAU option so we may not fully capture referral costs thus potentially underestimating cost-effectiveness. Another potential limitation is that the short follow-up period of 12 months may not capture the extent of the benefit that patients and the health system could gain through the availability of this service. For example, the degree to which the socioeconomic benefits and the returns to mental health associated with such interventions^76^ may not be fully evident by the 12-month end point. This is a common problem associated with trial-based economic evaluations.^77^

